## Abstract

**Background:**

Black women are significantly more likely to experience severe maternal morbidity and are 3 times as likely to die from pregnancy-related causes compared to White women. Using a strengths-based wellness approach within an integrated supportive care program provided by a community doula could offer pragmatic solutions for Black maternal disparities. The Protective Assets Reinforced with Integrated Care and Technology (PARITY) program consists of a wellness technology platform, including informational links to wellness content and reinforcing motivational SMS text messages, as well as community-based doula support delivered both in person and through the technology platform to improve Black maternal wellness.

**Objective:**

This pilot randomized controlled trial (RCT) and mixed methods evaluation aims to (1) determine the feasibility and acceptability of the PARITY intervention; (2) investigate the preliminary efficacy of the PARITY intervention on clinical outcomes (maternal blood pressure, gestational weight gain, and cesarean birth); and (3) investigate changes to wellness behavioral outcomes (nutrition, physical activity, sleep, and health care adherence) and empowered strengths (self-efficacy, social support, motivation, resilience, problem-solving, and self-regulation) in the intervention group compared to a control group.

**Methods:**

A 2-arm RCT and mixed methods evaluation will be conducted. Overall, 60 Black pregnant individuals will be randomized in a ratio of 1:1 to either the intervention or informational control group. Participants in the intervention group will receive access to the technology platform over a 12-week period that ends before birth. Intervention participants will be assigned a doula interventionist, who will meet with them 4 times during the intervention. All participants (intervention and control) will receive a referral for a birth doula at no cost, printed materials about having a healthy pregnancy, and community resources. Feasibility and acceptability will be assessed at the end of the program. Measures will be obtained at baseline (20-28 weeks), the 36th week of pregnancy, birth, and 6-12 weeks post partum. Summary statistics and distribution plots will be used to describe measured variables at each time point. A generalized linear mixed model with a shared random component will be used to analyze the effects of PARITY on clinical, wellness behavioral, and empowered strength outcomes, including baseline nutrition, physical activity, and sleep measures as covariates. For significant effects, post hoc contrasts will be adjusted using the Holm method to maintain comparison-wise error at or <.05. Missing data will be addressed using a pattern-mixture model.

**Results:**

The National Institute of Nursing Research funded this pilot RCT. Recruitment, enrollment, and data collection are ongoing, and the estimated study completion date is October 2024.

**Conclusions:**

The expected results of this study will provide the feasibility and preliminary efficacy of the PARITY intervention, to be used in a larger trial with a 12-month PARITY program intervention.

**Trial Registration:**

ClinicalTrials.gov NCT05802615; https://clinicaltrials.gov/study/NCT05802615

**International Registered Report Identifier (IRRID):**

DERR1-10.2196/58580

## Introduction

### Background

The United States spends more on health care than any other nation in the world yet has the highest maternal morbidity and mortality rates of all high-income nations [1,2]. Severe maternal morbidity, defined by the Centers for Disease Control and Prevention as maternal outcomes that result in significant or life-threatening consequences for a woman’s health, has increased by approximately 200% over the past 20 years, while maternal mortality has increased by 37% since 2018 [3-5]. Black women experience higher rates of pregnancy-related complications and are more likely to die from pregnancy or childbirth compared to White women, regardless of comorbid conditions or socioeconomic status [6-9]. This gap has not narrowed in decades, exposing Black families and their communities to profound emotional, social, and economic consequences that ripple for generations [10]. The effects of increased severe maternal morbidity in Black communities are wide ranging and include higher health service use, higher direct medical costs, extended hospital stays, long-term rehabilitation, ongoing chronic health conditions, disability, and earlier death [11-13].

Most studies regarding susceptible maternal populations commence from a deficit-based discourse, which refers to communication that focuses on deficiencies, lacks, or failures, ultimately perpetuating biases and hindering efforts to address disparities [14,15]. To counteract this deficit-based discourse, it is important to examine, include, and emphasize the strengths and protective assets of Black maternal populations [16]. An asset-based or strengths-based approach uses the positives of an individual, such as their knowledge, skills, and community, as the basis to create protective processes in health and well-being [14]. This study is an example of research designed using an asset-based approach [14], intentionally including measures and tools that elucidate the many strengths of Black maternal populations. This research is framed by the concepts of empowerment and wellness, which are principles of the midwifery model of care [17]. The use of a strengths-based approach helps buffer the deficit discourse participants may have internalized through previous interactions with health care services; highlights the assets of participants; and gives them tools for wellness that can be leveraged in confronting, overcoming, and maintaining resilience to risks within their lives.

Community-integrated care is a solution that empowers Black women to be healthy within the context of the neighborhoods and communities in which they live [18]. Community health workers (CHWs) are trusted members of their community who facilitate access to services and improve health care quality by providing community education, social support, and advocacy [19,20]. In our previous work, an intervention using a prenatal technology platform with CHW reinforcement translated to cost savings on health care use averaging US $1079 for intervention participants compared to control participants [21]. Doulas are a type of CHWs who are trained support persons and advocates who work with individuals during the pregnancy continuum and are uniquely situated to help overcome maternal health disparities [22,23]. Doula care has been shown to improve women’s experiences; is associated with improved maternal outcomes; and helps mitigate the effects of social determinants of health through better health literacy, social support, and cultural competence [22].

The theory of maternal adaptive capacity is a strength-focused theoretical framework that focuses on the protective assets one may use to achieve or maintain health throughout pregnancy [24]. On the basis of the theory of maternal adaptive capacity and our preliminary work, this randomized controlled trial (RCT) and mixed methods evaluation examines a novel, strengths-based intervention for pregnant Black women [21,24]. This intervention is entitled the Protective Assets Reinforced With Integrated Care and Technology (PARITY) program and consists of a wellness technology platform and community-based doula support. PARITY is a strengths-focused intervention that uses mobile technology and doula support to empower individual women to bolster their existing strengths (protective assets) to navigate the health care system, improve overall wellness behaviors, and improve maternal outcomes.

### Objectives

The overall purpose of this PARITY program is to reinforce protective assets through empowering messaging, promote wellness behaviors, and support Black birthing persons. This pilot trial will provide information on the feasibility, acceptability, and preliminary efficacy of the PARITY intervention among Black pregnant women as well as provide critical information on study design, retention, effect sizes, and outcomes assessment.

The objectives of this study are to (1) explore the feasibility and acceptability of the PARITY intervention; (2) investigate the preliminary efficacy of the PARITY intervention on changes to maternal blood pressure (primary), gestational weight gain, and cesarean birth (secondary) and estimate the effect size of the intervention relative to the control group; and (3) investigate changes to wellness behavioral outcomes (nutrition, physical activity, sleep, and health care adherence) and empowered strengths (self-efficacy, social support, motivation, resilience, problem-solving, and self-regulation) in PARITY intervention participants. With the combination of information, guidance, and support toward leveraging their innate strengths into actionable wellness, we hypothesize that the PARITY program will improve maternal blood pressure, gestational weight gain, and cesarean birth rate in the intervention group compared with the information-only control group. Further, we expect emphasizing individual strengths and building from them while navigating pregnancy-related health care will improve wellness behaviors and empowered strength variables such as adherence to medical care, including appointment adherence.

## Methods

### Study Design

This study is a 2-arm prospective RCT and mixed methods evaluation of the PARITY intervention for pregnant Black women. Participants will be randomized to either the information control group (30/60, 50%) or the intervention group (30/60, 50%) in a 1:1 ratio. A sample size of 30 participants per group provides 80% power to detect a significant difference at a .05 level while accounting for attrition [25-27]. Select intervention participants (10/60, 17% to 15/60, 50%) will engage in a qualitative interview at 12 weeks post partum to discuss their experiences, opinions, and suggestions for the intervention. Participants will be enrolled in the study for up to 24 weeks. This time frame will include enrollment, the intervention, and postpartum follow-up assessments. Due to the nature of the intervention, the participants, interventionists, and research assistants will not be blinded. However, standardized training and standard operating procedures, including the use of deidentified self-reported questionnaires administered at baseline and after the intervention period, will reduce the potential for bias due to not blinding.

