### Study Population

Participants will be included in the study based on the following criteria: (1) self-identify as being of Black race, (2) pregnant with gestational age 20 to 28 weeks at enrollment, (3) ability to read and write in the English language, (4) planning to give birth in a health care facility and receive obstetrical care with a health care record, (5) reside within 20 minutes of the identified metropolitan area, (6) 19 to 51 years of age, and (7) own a smartphone with internet access. Participants will be excluded from the study for the following reasons: (1) current involvement in another intervention study, (2) planned pregnancy termination, or (3) inability to provide informed consent.

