#### Qualitative Interviews

The qualitative interview uses the strengths-focused framework of the theory of maternal adaptive capacity to better understand the acceptability of the intervention and its role in emphasizing protective assets in Black pregnant women [24]. A total of 10 to 15 participants from the intervention group will be interviewed at 12 weeks post partum. A semistructured interview guide will be used to gather in-depth qualitative information. The interview guide consists of open-ended questions and additional probes that explore participants’ experiences and opinions regarding the various intervention components. The interviewer will have the flexibility to ask additional questions for further clarification and to ensure comprehensive understanding.

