### Recruitment

Prospective participants (intervention and control) will be recruited at the beginning of their pregnancy up to 28 weeks of gestation about interest and participation in the study. Participants will be recruited via advertisements on social media, fliers, and word of mouth. If an individual is interested in participating, they will contact the research team by completing the study screening questionnaire in REDCap or via telephone or email. Study personnel will contact the potential participant via telephone or email and explain the study in detail. Once interest is determined and screening eligibility is met, participants will be invited to sign a consent form and a medical release of information form and complete the baseline assessments at 20 to 28 weeks of pregnancy.

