All participants will complete postintervention surveys at 6 to 12 weeks post partum. At approximately 12 weeks post partum (or upon the receipt of records), participant medical records will be accessed to extract the pertinent outcome data. A total of 10 to 15 participants in the intervention group will be approached about completing the qualitative portion of the study. Participants will be approached in order based on the study’s completion date.

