### Outcome Measures

At enrollment, participants will sign a medical release of information form allowing the research team to measure data retrospectively from the participant’s medical records. To collect the self-report questionnaires for the enrollment and postpartum assessments, each participant will use a unique, secure link to complete the electronic questionnaires in REDCap at baseline after informed consent is signed and at 6 to 12 weeks post partum based on the participant’s due date. Reminders from the research team will be sent to participants using various forms of contact (phone and email) to complete the questionnaires as needed.

The following outcome measures will be used to examine the feasibility and acceptability of the PARITY intervention:

Feasibility will be assessed through enrollment, attrition, adherence to the intervention, and data collection.Enrollment rate: enrollment will be measured by the percentage of eligible individuals who agree to participate in the trial.Attrition rate: attrition will be measured by the percentage of eligible individuals who complete the study.Adherence to the intervention: adherence to the intervention will be measured using the Intervention Fidelity Checklist, where the doula interventionist will track when contact is made with participants and the number of doula sessions completed. Engagement with the platform will be tracked through clicks and the time spent on the platform.Data collection: data collection feasibility will be measured through study personnel’s sense of ease of use, time required, and missing data.Acceptability of and experiences with the intervention will be assessed using in-depth qualitative information gathered through interviews with intervention participants at 6 to 12 weeks post partum. Interviews will solicit (1) the usefulness of the intervention, (2) ideas to improve the intervention, (3) satisfaction with the intervention, and (4) the utility of innovative technology to deliver the intervention. The qualitative interviews will be audio recorded and transcribed verbatim.

The following outcome measures will be used to examine the preliminary efficacy of the PARITY intervention:

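### The stated 24-week maximum participation is too short: enrolment from 20 weeks' gestation with surveys 6 to 12 weeks post partum needs up to about 32 weeks

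*Protocol article*

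**What the plan says.** The Study Design section of the protocol article gives one figure for time on study and says what it covers: "Participants will be enrolled in the study for up to 24 weeks. This time frame will include enrollment, the intervention, and postpartum follow-up assessments".

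Other Methods sections fix the two ends of that period:

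- **Start.** Study Population requires participants to be "pregnant with gestational age 20 to 28 weeks at enrollment", and the Overview of the intervention repeats this range. Under Recruitment, those who consent "complete the baseline assessments at 20 to 28 weeks of pregnancy".
- **End, surveys.** Participant Allocation says: "All participants will complete postintervention surveys at 6 to 12 weeks post partum". Outcome Measures adds the anchor, placing the questionnaires "at 6 to 12 weeks post partum based on the participant’s due date".
- **End, interviews.** Qualitative Interviews says: "A total of 10 to 15 participants from the intervention group will be interviewed at 12 weeks post partum". Study Design and Outcomes also give 12 weeks, whereas Outcome Measures gives a range of 6 to 12 weeks.
- **Records.** Participant Allocation has medical records accessed at about 12 weeks post partum, or when they arrive. Outcome Measures says the release for this is signed at enrolment.

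No section has early enrollees wait before their time on study starts, or otherwise reconciles these windows with 24 weeks.

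**The concern.** A figure introduced by the words 'up to' should be the longest stay any participant can have. Here 24 weeks is the longest stay of the latest enrollee, who has the shortest pregnancy left. Someone enrolled at 20 weeks has about 20 weeks of pregnancy ahead, so 24 weeks on study would leave only about 4 weeks after birth. The survey window opens at 6.

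The article does not allow 24 weeks to be read as the active phase alone, because the next sentence says "This time frame will include enrollment, the intervention, and postpartum follow-up assessments".

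Two things could follow:

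- **The limit is applied.** The postpartum survey is the only post-baseline measurement of nutrition, physical activity, sleep and the six empowered strengths. It would be lost or squeezed according to gestational age at entry. Feasibility is judged partly on completion of the study, so these losses would also appear as attrition.
- **The limit is ignored.** Follow-up contact runs beyond the participation period that the article states.

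This pilot is meant to inform the design and retention plans of a larger trial, so the length of participation should be right.

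**Working it through.** **Inputs.**

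- Enrolment gestation E: 20 to 28 weeks (Study Population, Overview, Recruitment).
- Follow-up P: 6 to 12 weeks post partum (Overview, Participant Allocation), timed from the due date (Outcome Measures).
- Stated maximum: 24 weeks (Study Design).
- Gestation at birth or due date B: not given. I take 40 weeks and test 37 to 42.

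**Formula.** Time on study D = (B − E) + P.

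**Can 24 be reproduced?** Three routes give 24, but none gives it as a maximum over the stated windows:

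- Latest enrolment, latest follow-up: (40 − 28) + 12 = 24.
- Enrolment at 22 weeks, earliest follow-up: (40 − 22) + 6 = 24.
- A 12-week intervention plus 12 weeks post partum: 12 + 12 = 24. This leaves out any gap between the end of the intervention and birth.

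**Time needed with B = 40.** The last column is E + 24 − 40.

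| Enrolled at (weeks) | Survey window opens (study week) | Survey window closes (study week) | 24 weeks ends at (weeks post partum) |
|---|---|---|---|
| 20 | 26 | 32 | 4 |
| 22 | 24 | 30 | 6 |
| 24 | 22 | 28 | 8 |
| 26 | 20 | 26 | 10 |
| 28 | 18 | 24 | 12 |

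The range is therefore 18 weeks (enrolment at 28, survey at 6) to 32 weeks (enrolment at 20, survey at 12).

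**Who is affected with B = 40.** Setting D = 24 gives the threshold E = B + P − 24.

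- Window opens within 24 weeks: E of at least 40 + 6 − 24 = 22.
- Whole window within 24 weeks: E of at least 40 + 12 − 24 = 28.

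Enrolment before 22 weeks misses the window, enrolment from 22 to under 28 weeks gets part of it, and only enrolment at 28 weeks gets all of it.

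**Sensitivity to week of birth, if post partum is counted from the actual birth.**

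| Birth (weeks) | Maximum D (E = 20, P = 12) | 24 weeks ends, E = 20 (weeks post partum) | E needed to reach 6 weeks post partum | E needed to reach 12 weeks post partum |
|---|---|---|---|---|
| 37 | 29 | 7 | 19 (all enrollees) | 25 |
| 39 | 31 | 5 | 21 | 27 |
| 40 | 32 | 4 | 22 | 28 |
| 41 | 33 | 3 | 23 | 29 |
| 42 | 34 | 2 | 24 | 30 (none) |

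For 24 to be the true maximum for someone enrolled at 20 weeks and followed to 12 weeks post partum, birth would have to be at 24 − 12 + 20 = 32 weeks.

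**The case against.** The best defence is that the 24-week sentence is descriptive. Nothing makes it a withdrawal rule, a censoring date or a contact cut-off. The operational text under Participant Allocation and Outcome Measures points one way: controls are told to expect contact 6 to 12 weeks post partum, everyone completes the surveys in that window, and the questionnaires follow the due date. Staff who work from those sections would lose nobody. This stands, and it makes the misstated duration the likelier harm and lost data the conditional one. It does not make 24 weeks correct.

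A reader might be tempted to go further in four ways that the article does not support:

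- **That 6-week blood pressure is lost for early enrollees.** Blood pressure, weight and delivery mode are read retrospectively from the medical record under a release signed at enrolment. Nothing shown ties that release to 24 weeks.
- **That missingness related to gestational age at entry is built into the design.** It arises only if the summary sentence overrides the scheduling sections.
- **That 34 weeks is the required figure.** It assumes a birth at 42 weeks and a window that moves with the birth. The surveys are timed from the due date, so with a due date at 40 weeks a late birth leaves the survey maximum at 32.
- **That the consent form is wrong.** It is not shown.

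Two smaller points also stand. Interviews concern only 10 to 15 intervention participants, and one section allows them from 6 weeks. With birth at 37 weeks, even a participant enrolled at 20 weeks reaches 6 weeks post partum at study week 23, although the full window still runs to week 29.

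**Conclusion.** The stated maximum contradicts the article's own enrolment and follow-up windows. With a due date at 40 weeks, the schedule needs 18 to 32 weeks, so the figure is short by up to 32 − 24 = 8 weeks. For a participant enrolled at 20 weeks, it falls 2 weeks before the survey window opens. The 40-week due date is an assumption, but the direction does not depend on it: the maximum exceeds 24 weeks at each birth week tested from 37 to 42.

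The conflict rests on the postpartum surveys and, for some participants, the interview. Outcomes taken from the medical record are not shown to be affected, and the power calculation is untouched. Loss of surveys by gestational age at entry is a consequence only if the limit is enforced. This is a definite error in a design figure, worth correcting but not a threat to the main clinical comparison.

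**What to change.** In Study Design, restate the maximum participation as about 32 weeks, defined as 20 weeks' gestation to 12 weeks after a due date at 40 weeks. If the intention is to count 12 weeks from the actual birth, say so and allow up to 34 weeks for a birth at 42 weeks.

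Reconcile the figure with Study Population, the intervention Overview, Qualitative Interviews, Participant Allocation and Outcome Measures, including the two different timings given for the interview. Check that the consent form states the same duration.

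The cost is one figure and a clarifying phrase in the protocol, plus a minor ethics-board modification if the approved protocol or consent form repeats 24 weeks. No analysis or sample-size change is needed.

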Maternal blood pressure (primary) at 20 weeks, 36 weeks, birth, and 6 weeks post partum will be measured retrospectively from the medical record at 12 weeks post partum. The data will be analyzed as a continuous variable using the participant’s blood pressure (systolic and diastolic) as well as categorically with the blood pressure classifications of hypertension (>140/90) and severe hypertension (>160/110).Gestational weight gain (secondary), or the amount of weight gained in pounds at 20 weeks, birth, and 6 weeks post partum, will be measured retrospectively from the medical record at 12 weeks post partum.Cesarean birth (secondary) will be assessed from the delivery modality (vaginal, cesarean, or assisted vaginal delivery), measured retrospectively from the medical record at 12 weeks post partum.Perinatal outcomes (exploratory) from birth will be measured retrospectively at 12 weeks post partum via the maternal medical record. The perinatal outcomes that will be measured include preterm delivery; gestational diabetes; birth weight; gestational age at delivery; anesthesia used during labor; labor length; delivery provider type (obstetric physician, family physician, resident physician, or certified nurse midwife); and intrapartum medical diagnoses according to theInternational Classification of Diseases, 10th Revision[34], including hypertensive disorders of pregnancy, intrapartum fever, and postpartum hemorrhage. In addition, the Appearance, Pulse, Grimace response, Activity, and Respiration score of the newborn at birth will be measured as a way to summarize the health of the baby [35].

The following outcome measures will be used to investigate changes to wellness behavioral outcomes and empowered strengths:

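### The reason given for leaving research assistants unblinded does not extend to extracting blood pressure and weight from charts, and the one safeguard named does not reach those outcomes

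*Protocol article*

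**What the plan says.** Study Design gives one reason for three unblinded groups: "Due to the nature of the intervention, the participants, interventionists, and research assistants will not be blinded". It then names what should limit the resulting bias: "standardized training and standard operating procedures, including the use of deidentified self-reported questionnaires administered at baseline and after the intervention period".

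The clinical outcomes come by another route. Under Outcome Measures, "Maternal blood pressure (primary) at 20 weeks, 36 weeks, birth, and 6 weeks post partum will be measured retrospectively from the medical record". Weight gain and mode of birth are likewise "measured retrospectively from the medical record at 12 weeks post partum". The same section describes a signed release "allowing the research team to measure data retrospectively from the" participant's records. Participant Allocation places this at about 12 weeks post partum or on receipt of the records, when "participant medical records will be accessed to extract the pertinent outcome data". Neither section names the role that does the extraction, and neither says whether that person knows the arm.

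The only other masking statement, under Doula Sessions, keeps outcome data from the doula. It does not keep allocation from whoever extracts outcomes.

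**The concern.** What the intervention consists of explains why participants and the doula know the arm. It does not explain why someone reading a chart months later must know it. The platform component ends before birth, and the record is read about 12 weeks after birth. Masking this step is feasible, yet the stated reason covers research assistants as a group without separating their duties.

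The mitigation sentence adds to the problem because it speaks of bias from not blinding in general. A reader could take the primary outcome to be covered, whereas the only concrete measure named has no bearing on it.

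At stake is the blood pressure comparison. The Objectives section states a directional hypothesis and asks for an effect size, and the results are to inform a larger trial. If someone who knows the arm has to choose between recorded values, that choice can move both the estimate and the categorical result. Outcome Measures also classifies blood pressure at 140/90 and 160/110, so choosing between readings near a cut-off can change a participant's category.

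**Working it through.** **Step 1. Match each safeguard to the outcomes it can reach.**

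| Outcome | Source in the article | Reached by the questionnaires? |
|---|---|---|
| Blood pressure (primary) | Medical record | No |
| Gestational weight gain (secondary) | Medical record | No |
| Cesarean birth (secondary) | Medical record | No, but little discretion in reading it |
| Nutrition, activity, sleep, empowered strengths | Self-administered in REDCap | Yes |

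Deidentification appears under Ethical Considerations as a confidentiality measure. It removes the name and is not said to conceal the arm. Training and operating procedures could in principle cover chart extraction, but the article does not say that they do.

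**Step 2. Establish what is stated and what is inferred.** Stated: research assistants are unblinded, the research team takes data from the records, and the research coordinator tells participants their assignment. Not stated: who extracts the chart data. That the extractor is unmasked is therefore an inference, from a general statement with no exception for this step.

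**Step 3. Reproduce the plan's own figure.** The sample size section uses a two-tailed Welch *t* test at .05 with 80% power. With equal variances and equal groups, df = 2n − 2 and the noncentrality is d × √(n/2).

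- n = 25, d = 0.81: noncentrality 0.81 × √12.5 = 2.86, df = 48, power 80.1%.
- n = 20, d = 0.91: noncentrality 0.91 × √10 = 2.88, df = 38, power 80.1%.

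Both stated differences, 0.81 SD and 0.91 SD, reproduce. This point does not dispute them.

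**Step 4. Illustrate the sensitivity of the comparison.** The documents give no figure for extraction bias. Assume no true effect and a shift of b SD in one arm caused by the choice of readings. The two-sided rejection rate is then the power of the same test at d = b.

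| Assumed shift b | Share of 0.81 SD (b / 0.81) | 20 per group | 25 per group | 30 per group |
|---|---|---|---|---|
| 0 | 0% | 5% | 5% | 5% |
| 0.1 | 12% | 6.1% | 6.4% | 6.7% |
| 0.2 | 25% | 9.5% | 10.7% | 11.9% |
| 0.3 | 37% | 15.2% | 18.0% | 20.8% |

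For example, b = 0.2 at 25 per group gives noncentrality 0.2 × √12.5 = 0.71 and a rejection rate of 10.7%. The calculation uses the *t* test of the sample size section, not the mixed model planned for the analysis, so it shows the order of magnitude only.

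**The case against.** The strongest reply has four parts.

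- **The safeguard is broader than questionnaires.** Training and operating procedures come first in the sentence, and the questionnaires are an example. This stands. A reader might infer that questionnaires are the whole safeguard, but the text does not say so. Nor does it say that they protect blood pressure. For self-report outcomes, self-administration does limit staff influence, so that part of the sentence deserves to be kept.
- **No unmasked extractor is named.** This also stands. A reader might infer that someone who knows the arm will choose the readings. The documents show only that research assistants are unblinded and that this step is not masked.
- **The room for bias is limited.** This stands in large part. The readings come from routine obstetric records, so the exposure lies in selection and classification, and mode of birth leaves almost no choice. A reader might add that any such bias could never be found. It could: a masked second extraction from the same records would reveal it, at least until personal health information is removed at study completion. None is described.
- **A condensed article may omit extraction detail.** This is right for the rule on which reading counts, whose absence alone is no finding. It does not answer the point about blinding, which rests on the reason and the mitigation that the article itself states.

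A larger size is also tempting. The expected lowest of three normal readings lies 0.846 SD below their mean, so an assumed within-visit SD of 6 to 8 mmHg gives 0.846 × 6 = 5.1 to 0.846 × 8 = 6.8 mmHg. The documents support neither three readings nor that SD. The figure also requires always taking the lowest reading in one arm and the mean in the other, which is close to deliberate manipulation. It is a ceiling, not an estimate.

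**Conclusion.** The point holds in a limited form. The stated reason for not blinding does not apply to chart extraction, the article does not mask that step, and the only safeguard it names concretely does not reach the chart outcomes. Blood pressure is the outcome chiefly exposed, with weight next.

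The size of any bias is unknown. The rise in rejection rate from 5% to about 6% to 18% at 25 per group rests wholly on the assumed shift of 0.1 to 0.3 SD and on the inference that the extractor would know the arm. This is a pilot for feasibility and preliminary efficacy, so the matter is moderate. It is worth correcting because the remedy costs little and the effect estimate is meant to be carried forward.

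**What to change.** In Study Design:

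1. Limit the unblinded roles to participants, the interventionist and the staff who handle allocation.
2. State that an existing team member not involved in allocation will extract the chart outcomes by study ID, with the group field hidden in REDCap, using the same reading-selection rule in both arms.
3. Keep the reference to training and operating procedures, and limit the questionnaire part of the mitigation sentence to the self-report outcomes.

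If no team member is unaware of allocation, state plainly that extraction is unmasked.

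The cost is a user-rights setting, a few changed sentences and a small reallocation of duties for 60 charts. No extra staff are needed if duties can be split within the team; the article does not show whether they can. Sample size, visits and clinical care are unchanged.
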